### Data collection

#### Epidemiological data

No active recruitment of dengue cases is planned, as the information on the incidence of dengue during the overall study period in both control and intervention clusters is extracted from the national e-Dengue surveillance database. For each confirmed dengue case, demographic data, signs and symptoms at first medical visit, date of diagnosis, results of the rapid dengue COMBO test, hospitalization, and vital status at discharge are extracted.

#### Entomological data

Entomological data for the assessment of secondary outcomes are collected in 12 clusters randomly selected from each arm (24 in total) and stratified by socio-economic status (medium versus low cost).

#### Climatic parameters

Common climatic parameters (rainfall, temperature, and humidity) have been reported to influence the intensity and magnitude of dengue incidence [27–29]. These parameters will be requested from the Malaysian Meteorological Department, Ministry of Energy, Science, Technology, Environment and Climate Change for two points: Petaling Jaya and Kuala Lumpur International Airport.

### Monitoring *Aedes* population densities

The density of *Aedes aegypti* and *Ae. albopictus* populations will be monitored monthly throughout the study period using larval and adult collection methods in a sample of 12 clusters per arm. Larval surveys are carried out using a minimum of 40 ovitraps per cluster. Each ovitrap consists of a 250-ml cylindrical, black plastic container (7.5 cm diameter, 9.0 cm height, 300 ml volume) filled with tap water to a depth of 5.5 cm and is equipped with a removable oviposition paddle made from a thin strip of brown hardboard (10 cm × 2.5 cm × 0.3 cm). Larval surveys start 5 weeks before the start of the intervention to measure the baseline density. Ovitraps are positioned randomly in spaces with minimum human, physical, and environmental disturbance: (a) in the semi-indoor environment—defined as the area outside of the housing units but still sheltered by the roof (e.g. shared corridor and stairway), (b) in partially or totally shaded outdoor areas (e.g. near bushes, small plants, and temporary structures), and (c) indoor (under the sofa, dining table, sink, bed, working / study desk) only in the apartments of those who volunteer to have them.

To determine the OI, all ovitraps are collected once a week and replaced by new ones with fresh tap water and egg-free oviposition paddles. The collected ovitraps are brought back to the IMR laboratory (Kuala Lumpur) for further processing. Ovitrap contents and oviposition paddles are transferred into plastic containers and labelled with the name of the cluster and date of collection. Larvae emerged from the eggs laid in the ovitraps undergo species identification [30, 31] using a compound microscope (Nikon Eclipse® E100, Japan).

To determine the CI, a minimum of 20 suspected mosquito breeding containers within 50 m radius of the study cluster are examined once a month in each cluster. Larval samples from the positive containers are collected in a sample bottle and brought back for identification. The larvae are allowed to emerge into adults for morphological identification.

To monitor adult mosquito densities, monthly surveys are carried out with sticky ovitraps, i.e. a modification of conventional ovitraps as described by Lau et al [32]. The inner wall of the ovitrap is lined with a 5.5 cm × 24 cm transparent plastic sheet. The inner plastic sheet is covered with insect glue (Neopeace, ACM, Malaysia) attached to the container using adhesive tape on both sides of the top of the container. A hole is drilled about 3 cm above the bottom to avoid flooding of the trap with rain water. A total of 50–200 sticky ovitraps are deployed in the study area, in every alternate floor with emphasis on dark and humid areas such as garbage rooms, emergency exits, shoe racks, and vegetation considered as *Aedes* resting places. The adult samples are isolated in a single vial and send for identification.

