#### Community engagement

Community engagement (CE) starts at the time of baseline data collection and is maintained throughout the study period by a team specially trained in CE activities. The main objectives of this activity are to create public awareness and trust and to increase their participation during and following the deployment of the intervention. The first step of CE activities consists of an appointment with the community leaders in each cluster through phone calls using a standard script in order to schedule a face-to-face meeting. The purpose, objectives, procedure, and timelines of the iDEM trial are presented to community leaders followed by a question-and-answer session. Information on demographic and architectural characteristics such as number of buildings, number of floors per building, number of units per floor, total number of occupants, parking lots, and public facilities (gymnasium, kindergarten, shops, restaurants, swimming pool, and playground) of the cluster are recorded after the briefing. A second meeting involving the residents is organized upon the community leader request. Information, education, and communication material such as banners, posters (Additional file 3), and brochures are distributed to explain the objectives of the study and the role of the community during and following the deployment of the intervention. Softcopy of these materials is sent to the building managers through email or WhatsApp message and subsequently disseminated among the community. A notification is sent to the building manager one week before the deployment of the intervention to remind them of the date and details about the intervention.

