### Outcomes

The primary outcome measure is the estimated dengue incidence rate in both control and treatment clusters. The number of confirmed dengue cases is provided by the e-Dengue system (http://spwd.arsm.gov.my).

Dengue is a notifiable disease in Malaysia. All clinically suspected or confirmed dengue cases are notified by the medical officer to the nearest District Health Office within 24 h (Additional file 1). Currently, dengue confirmation is based on dengue rapid combo test for (1) qualitative detection and differentiation of specific IgG and IgM antibodies to dengue virus in human serum and plasma and (2) dengue rapid NS1 test for qualitative detection of dengue NS1 antigen in human whole blood, serum, and plasma [23]. Further laboratory tests are performed if necessary (under clinical management not determined by the current trial). The e-Dengue case definition is based on the international classification of diseases ICD (10: A90, A91) and positive diagnostic results of either NS1, IgM, or IgG or any combination of test results [24]. Since 2014, all cases reported in Malaysia are confirmed cases.

Secondary outcomes measures include:
Ovitrap index (OI): number of positive ovitraps divided by the total number of recovered ovitraps.Larval index (LI): number of larvae identified divided by the number of ovitraps recovered.Container index (CI): proportion of water-holding surveyed containers infested with *Aedes* larvae or pupae.Adult survey: mean number of female adults *Aedes* collected in sticky ovitraps.Resistance to deltamethrin: measurement of knock-down and mortality rates in wild strain adult mosquito populationResidual activity of deltamethrin measured by wall deposit bioassays [25]

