### Allocation

The random allocation of the clusters to the control or the intervention arm (1:1 ratio) was carried out using the PLAN procedure of SAS software, version 9.4 (Copyright (c) 2002-2012 by SAS Institute Inc., Cary, NC, USA), and was stratified on the economic level of the clusters (low or medium) because this is associated with dengue incidence.

In each stratum, clusters were randomly numbered and block randomization were carried out with block sizes of 10 and 16 in order to allocate the clusters to the intervention or control arm. Randomization was carried out after the protocol was approved by the IMR Research Committee.

This trial is not blinded. All clusters were allocated at the start of the trial so an allocation concealment mechanism is not required. Dengue outbreaks are common in Malaysia and controlled by reactive vector control activities. Therefore, discontinuing or modifying the allocated interventions in case of unexpected dengue outbreak was not planned. The allocation sequence has been generated by a statistician of the Service of Biostatistics of Hospices Civils de Lyon, France. The code written by this first statistician was double-checked by a second statistician in regard to the conformity to the randomization protocol. The list of clusters in each arm was saved in a text file and transmitted to the investigators (IMR-Malaysia).

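### The ovitrap index pools indoor traps placed only with volunteers, so an indoor share that differs by arm or drifts over time could shift it without any change in mosquitoes

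*Protocol article*

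**What the plan says.** All references are to the protocol article.

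- **Trap placement** (Monitoring Aedes population densities): "Larval surveys are carried out using a minimum of 40 ovitraps per cluster". Traps go to three kinds of site: semi-indoor, shaded outdoor and indoor. Indoor traps are placed "only in the apartments of those who volunteer to have them". No number or share per site type is given.
- **Outcome** (Outcomes): OI is the "number of positive ovitraps divided by the total number of recovered ovitraps", with no distinction by site. Secondary outcome names OI as the main secondary outcome.
- **Order of events** (Allocation; Entomological data): "All clusters were allocated at the start of the trial so an allocation concealment mechanism is not required". The trial is not blinded, and the 12 entomology clusters per arm are sampled from within the allocated arms.
- **Engagement** (Interventions; Community engagement): active community engagement is listed with spraying and trap deployment as part of the intervention strategy. Its aims are "to create public awareness and trust and to increase their participation during and following the deployment of the intervention".
- **Baseline** (Monitoring Aedes population densities): "Larval surveys start 5 weeks before the start of the intervention to measure the baseline density".
- **Analysis** (Secondary outcome): OI is compared as a risk difference from a least-squares model with robust standard errors. No site-type term is named. Adjustment for the baseline value is stated for larval counts; OI is estimated over the baseline and intervention periods, but no matching adjustment is stated.

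**The concern.** A pooled proportion depends on positivity within each type of site and on how the traps are divided among the types. Randomisation protects the comparison only if that division does not respond to allocation. Here one of the three site types depends on residents agreeing to host a trap, in a trial where allocation is open and one arm receives a programme intended to build trust and participation. If that programme makes residents readier to accept a trap at home, or keeps them hosting for longer, the indoor share will differ between arms or diverge over the two years.

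At stake is the reading of the main secondary outcome. A difference in OI produced by trap location would be read as an effect on *Aedes* density. The larval count per ovitrap comes from the same traps and carries a weaker form of the same risk.

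**Working it through.** **1. Does recruitment follow allocation?** No recruitment date for trap hosts is given. All clusters were allocated at the start, and the entomology clusters were drawn from each arm. Hosts in those clusters were therefore apparently recruited after allocation. This is an inference.

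**2. Does a driver of volunteering differ by arm?** The Interventions section gives active engagement to the intervention arm, and both arms receive routine health education. The Community engagement section refers to each cluster without naming an arm, so the one-arm reading rests on Interventions.

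**3. Does the baseline precede the driver?** Engagement starts with baseline data collection. Table 1 shows it from November 2019 and ovitrapping from February 2020. The trap mix may already differ at baseline.

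**4. Size of the shift.** Let s be the indoor share of recovered traps, and let p_in and p_other be the positivities, the same in both arms (no mosquito effect). Then

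OI = s × p_in + (1 − s) × p_other

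OI difference = (s_I − s_C) × (p_in − p_other)

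The documents give none of these inputs, so the values below are assumptions.

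| Share difference | Gap 10 points | Gap 20 points | Gap 30 points |
|---|---|---|---|
| 10 points | 1 | 2 | 3 |
| 20 points | 2 | 4 | 6 |

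Entries are percentage points of OI. With 40 traps, a 10-point share difference is 0.10 × 40 = 4 traps per cluster.

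Worked case, indoor less often positive: p_in = 10%, p_other = 40%, shares 30% (intervention) and 10% (control).
- Intervention: 0.30 × 0.10 + 0.70 × 0.40 = 0.31
- Control: 0.10 × 0.10 + 0.90 × 0.40 = 0.37
- Difference: −6 points

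Reverse case, same shares: p_in = 30%, p_other = 20%.
- Intervention: 0.30 × 0.30 + 0.70 × 0.20 = 0.23
- Control: 0.10 × 0.30 + 0.90 × 0.20 = 0.21
- Difference: +2 points

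If p_in = p_other, the difference is zero whatever the shares.

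**5. What baseline data can remove.** In a change-from-baseline comparison the remaining shift is the difference between arms in the change of indoor share, times the gap. Shares of 20% and 10% throughout leave nothing. If both arms start at 10% and the intervention arm rises to 20%, the full 2 to 3 points (gap 20 to 30) remain. Baseline data therefore deal with a constant imbalance but not with drift.

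**6. Illustration of error rate.** The simulation used 12 v 12 clusters, 40 traps, 100 weeks, no mosquito effect and non-indoor positivity of 40%. Gaps were 10 to 30 points, and the test was an unadjusted t-test on cluster OI. The test stands in for the planned model, and the between-cluster SDs are assumed.

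| Indoor share, control v intervention | False-positive rate, SD 5 points | False-positive rate, SD 10 points |
|---|---|---|
| 20% v 20% | 4.3–5.2% | 5.0–5.8% |
| 10% v 20% | 7–28% | 5–11% |

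Equal shares restore the nominal 5%. The other rates show what the assumptions imply and say nothing about what has happened in this trial.

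**The case against.** **Site type is lost.** Containers are "labelled with the name of the cluster and date of collection", and a reader might infer that trap location goes unrecorded, so that no adjustment is possible. The article does not support this. It does not say the label carries nothing else. The Data management section describes paper entomology forms, checked after entry, whose fields are not shown.

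**The mix is uneven.** A reader might take the absence of a quota to mean that numbers per site type vary. The article sets no quota, but it condenses a fuller protocol that may. What stands is that indoor placement depends on volunteers, which a quota for the other site types would not change.

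**The baseline takes care of it.** Five weeks of trapping come first, and larval counts are adjusted for baseline. It would therefore be wrong to say that larval counts share the problem in full. The objection is weaker for OI, where no such adjustment is stated, and it does not cover drift in either outcome.

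**The causal path is indirect.** Engagement aims at participation in the intervention rather than in monitoring. It works largely through community leaders and building managers, with a residents' meeting only on request. This is fair, and it is why the point is put as a possibility.

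**Size and sign are assumed.** This is correct. A reader might infer a bias that favours the intervention; the documents do not support that direction or any other.

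**Conclusion.** The concern holds as a risk to the main secondary outcome. The article lets one component of the trap mix depend on volunteering, apparently after open allocation and with active engagement in the intervention arm. It then pools all traps into OI and describes an analysis with neither a site-type term nor a stated baseline adjustment.

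The shift is the share difference times the positivity gap: 2 to 6 points under assumed share differences of 10 to 20 points and gaps of 20 to 30 points, of unknown sign, and zero if positivity does not vary by site. The mechanism also needs the indoor share actually to differ or drift, which the documents neither show nor exclude. Larval counts are affected to a lesser extent. Primary dengue incidence comes from surveillance data and is untouched.

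**What to change.** 1. Set the same number of semi-indoor traps and the same number of outdoor traps in all 24 clusters.
2. Record a site-type code for every trap, on the label or the form, if this is not already done.
3. Adjust the OI and larval-count analyses for site type, or standardise them. For OI, compute Σ w_k × p_k over site types k with the same weights w_k in both arms.
4. State baseline adjustment for OI, as is already stated for larval counts.
5. Add a sensitivity analysis restricted to non-indoor traps, and report the indoor share by arm and over time. Site-type adjustment removes the effect of the mix but not any difference between arms in which households volunteer; this analysis addresses that.

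Making the non-indoor traps the main analysis set is not advised. Spraying and devices are applied mainly in corridors and other semi-indoor places, so that set would measure density largely where the intervention acts and would drop the living space.

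The cost is slightly more recording and analysis work. If the forms already hold trap location, the analysis changes need no new data.

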### Monitoring mosquito resistance

#### Adult bioassay test

We will measure susceptibility levels to deltamethrin in the field population. The test will follow the WHO protocol [33]. Pyrethroid resistance monitoring is conducted on sugar-fed adult female mosquitoes aged 3 to 5 days against a diagnostic concentration (0.03% deltamethrin, 0.25% permethrin, 0.15% cyfluthrin, and 0.03% lambda-cyhalothrin), which is used to impregnate paper at the recommended exposure time. Five replicates of 20 adult field strain mosquitoes from the 24 clusters selected for entomological endpoints are prepared. Two replicates of susceptible mosquitoes from the insectary laboratory of IMR are used as control strains. The cumulative knockdown counts are recorded every minute within the exposure period of 1 h, or until 90% knockdown is observed. After the exposure period, all the tested mosquitoes (live and knocked down) are transferred into holding tubes for a 24-h recovery period and supplied with 10% sugar solution in cotton balls. Adult mortality is then recorded. If the mortality rate in the control group is between 5 and 20%, the percentage of mortality in the exposed mosquitos is corrected by using Abbot’s formula [33]. Surviving mosquitoes are transferred into Eppendorf tubes and kept at − 80 °C for enzyme micro-assay.

#### Enzyme micro-assay

Three enzyme assays, namely mixed function oxidase [34, 35], esterase [35, 36], and insensitive acetylcholinesterase [35] are conducted in sugar-fed female mosquitoes, aged 3–5 days, to determine the enzyme activity. The female mosquitoes are raised from eggs collected in the field. The same homogenate of an individual mosquito is used to assess all three enzyme assays.

### Monitoring quality of TORS and ADDs post-application

The quality control monitoring for ORS was conducted in 4 clusters using a susceptible laboratory strain mosquito, resistant laboratory strain mosquitoes, and a wild field strain mosquitoes of *Aedes aegypti*. To assess post-application quality of K-Othrine® Polyzone spray, wall deposit bioassays are conducted 48 h after spraying and repeated every 3 weeks for a period of 4 months [25]. Standard WHO bioassay cones are firmly positioned onto the TORS treated wall in a perpendicular position using masking tape. Ten adult female mosquitoes (sucrose-fed, 3–5 days old, non-blood fed) are introduced into the bioassay cone for 30 min through the aperture using a battery-operated aspirator, and then collected back and observed for 24 h mortality. Three biological replicates of 10 mosquitoes are prepared for laboratory and field strains of *Aedes aegypti*. Residual effect of K-Othrine® Polyzone is determined by evaluating the knock down time and mortality rate. Knock down is observed for 30 min at 1-min intervals. After exposure, the mosquitoes are aspirated out, transferred to paper cups, held at 27 ± 2 °C with 75 ± 10% relative humidity and sugar-fed. The mortality is recorded 24 h after testing. The level of resistance is evaluated using the WHO criteria [33].

To assess ADD quality post-application, the presence/absence and estimated quantities of mosquito larvae in the water inside the ADDs are recorded at each service. The water was collected from randomised ADD (3 ADDs) in study sites and tested using laboratory strain of *Aedes aegypti*. Every month, 250 ml water samples are taken from three randomly selected deployed ADDs that are positive for *Aedes* larvae and brought back to the laboratory to confirm the presence and activity of the pyriproxyfen larvicide. In each 250 ml ADD water sample, 25 third instar (L_3_) larvae from the IMR rearing colony of *Aedes aegypti* are added [33]. Emergence of mosquito adults is monitored every day until all larvae have emerged or died or all larvae from control emerge into adult. An emergence rate of adult mosquito less than 10% is indicative of adequate pyriproxyfen quality in the ADD water sample. The samples are collected at the same time as the Container Index sampling and are used for quality control of the ADD and as positive control for the auto-dissemination testing.

To assess auto-dissemination efficacy of the ADDs, water samples of nearby containers are assessed for pyriproxyfen content. The *Aedes*-positive samples from natural containers collected for the CI (as explained above) are used to monitor larval development. Per 10 ml water sample collected, one susceptible strain larvae (L_3_, *Aedes aegypti*) is added to the water. Emergence of adults is monitored every day until all larvae have emerged or died. Significant reductions in adult mosquito emergence rates (i.e. high rates of larval/pupal mortality) in the intervention cluster samples compared to the control cluster samples is indicative of pyriproxyfen autodissemination from the ADDs.

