### Secondary outcome

The main secondary outcome will be the OI. The latter will be estimated over the baseline and intervention period in the 24 clusters selected for entomological monitoring. To quantify the effect of the interventions on the proportion of positive ovitraps, a modified ordinary least squares regression model using a robust standard error estimator will be implemented [21]. Using this model, the effect of the interventions will be quantified by the estimation of a difference of risk with its 95% confidence interval. This analysis will be carried out for both species overall and for each of the two species of mosquito separately.

Larval count per ovitrap (LI) will be estimated in the 24 clusters selected for entomological monitoring over the baseline and intervention period. A negative binomial regression will be used with the number of larvae as the response variable. The analysis will be adjusted by the baseline measurement of the outcome. Using this model, the effect of the interventions will be quantified by the estimation of a ratio of means with its 95% confidence interval. This analysis will be carried out for both species overall and for each of the two species of mosquito separately if possible.

The adult population will be estimated by counting the number of adult female *Aedes* mosquitoes collected with sticky ovitraps during the study. The total number of adult females will be divided by the number of sticky ovitraps used to obtain the mean number of adult females.

The emergence rate, defined as the proportion of larvae that emerge as adult mosquitoes, will be estimated in each arm and compared between the two arms using the chi-squared test or the Fisher exact test. This analysis will be carried out for both mosquito species combined and for each species separately.

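### The emergence comparison for auto-dissemination pools larvae by arm: containers get unequal weight, and the test treats larvae from one container and locality as independent

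*Protocol article*

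**What the plan says.** All references are to the protocol article.

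- **Seeding of natural containers** (Monitoring quality of TORS and ADDs post-application). *Aedes*-positive "samples from natural containers collected for the CI (as explained above) are used to monitor larval development". The seeding rule is "Per 10 ml water sample collected, one susceptible strain larvae", using third-instar *Ae. aegypti*. A significant fall in emergence in intervention samples relative to control samples is taken as indicating auto-dissemination.
- **Seeding of trap water** (same section). "In each 250 ml ADD water sample, 25 third instar (L_3_) larvae from the IMR rearing colony of *Aedes aegypti* are added". Here both the volume and the larva number are fixed. These samples also serve as the positive control for the auto-dissemination test.
- **How natural containers are sampled** (Monitoring *Aedes* population densities). Every month the survey inspects 20 or more suspect containers for each locality. On the handling of those found positive, the text says: "Larval samples from the positive containers are collected in a sample bottle and brought back for identification". No volume is stated.
- **Analysis** (Secondary outcome). "The emergence rate, defined as the proportion of larvae that emerge as adult mosquitoes, will be estimated in each arm", and the two arms are compared by chi-squared or Fisher exact test, for both species combined and for each separately. No container or cluster term is mentioned.
- **Clusters** (Entomological data). Twelve clusters per arm, 24 in total.

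**The concern.** The question is whether breeding sites near the traps received pyriproxyfen, so the natural unit of observation is the container and the randomised unit is the locality. The stated analysis uses the larva. Two things follow.

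1. **Weighting.** With seeding at a fixed density and no fixed volume, a container's share of the arm-level rate is its share of the water collected. Nothing in the plan says this weighting is wanted. It matters if containers that give more water respond differently. Correcting the standard error for clustering while still pooling larvae would leave the weighting unchanged.
2. **Test.** Larvae in one container share the same water, and containers in one locality share the same allocation and environment. A chi-squared or Fisher test on larvae ignores both and gives p values that are too small.

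This is the only test described for larvicide transfer to surrounding containers, and it is read through a significance criterion. An estimate that depends on container volume, with an overstated p value, is a weak basis for a statement about mechanism in either direction.

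**Working it through.** The plan gives no sample size, power or effect for this comparison, so there is no figure to reproduce. All container volumes, emergence rates and correlations below are assumptions.

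**Step 1: is the seeding rule a density?** Trap water: 25 / 250 ml = 0.1 larva per ml. Natural containers: 1 / 10 ml = 0.1 per ml. The match favours reading the rule as a density. If it instead means a single 10 ml sample with one larva per container, containers are weighted equally and only the clustering by locality remains.

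**Step 2: the weighting.** With V the volume collected from a container and e its emergence proportion, the pooled rate is ΣVe / ΣV and the container mean is Σe / (number of containers). They agree if V is constant, or if e is unrelated to V.

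**Step 3: illustration.** Assume half the containers are small, control emergence is 0.90, and treated small containers have 0.20.

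| Collected ml (small / large) | Emergence in treated large | Pooled rate | Pooled difference | Container-mean difference |
|---|---|---|---|---|
| 100 / 100 | 0.90 | 0.550 | 0.350 | 0.350 |
| 50 / 250 | 0.90 | (2.5×0.2 + 12.5×0.9)/15 = 0.783 | 0.117 | 0.350 |
| 50 / 500 | 0.90 | (2.5×0.2 + 25×0.9)/27.5 = 0.836 | 0.064 | 0.350 |
| 50 / 500 | 0.60 | (2.5×0.2 + 25×0.6)/27.5 = 0.564 | 0.336 | 0.500 |

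The attenuation runs from none to severe, depending on inputs that the documents do not give.

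**Step 4: simulation of estimate and test.** Twelve clusters per arm, 4 positive containers per cluster, 2000 runs. Container volume is log-normal with median 200 ml. Baseline emergence is 0.85 with within-container correlation 0.1 and no extra locality correlation. With transfer, 30% of intervention containers receive a fixed dose that dilutes with volume; at 200 ml it multiplies emergence by 1/(1 + 1.5) = 0.4. The pooled chi-squared test is compared with a t-test on cluster means of container proportions.

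| Volume collected | Log-SD of volume | Difference: pooled / cluster means | Reduction declared with transfer: pooled / cluster means | Reduction declared with no transfer: pooled / cluster means |
|---|---|---|---|---|
| Whole content | 0.3 | 0.148 / 0.153 | 1.00 / 0.93 | 12.4% / 2.7% |
| Whole content | 1.0 | 0.100 / 0.149 | 0.95 / 0.88 | 24.1% / 2.4% |
| Whole content | 1.5 | 0.060 / 0.145 | 0.77 / 0.82 | 34.8% / 2.7% |
| Capped at 250 ml | 0.3 | 0.149 / 0.152 | 1.00 / 0.93 | 12.1% / 2.2% |
| Capped at 250 ml | 1.0 | 0.128 / 0.149 | 0.98 / 0.88 | 13.9% / 2.9% |
| Capped at 250 ml | 1.5 | 0.110 / 0.144 | 0.96 / 0.80 | 12.9% / 2.3% |

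The nominal rate in the last column is 2.5% (the benefit direction of a two-sided 5% test).

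**Step 5: hand check of the false-positive rate.** With about 20 larvae per container (200 ml) and correlation 0.1, the design effect is 1 + 19 × 0.1 = 2.9. The chance of crossing 1.96 in one direction is P(Z > 1.96/√2.9) = P(Z > 1.15) ≈ 12.5%, in line with the 12.4% simulated at the smallest volume spread. Wider spread makes the larva counts more unequal and raises it. Any locality correlation would raise it further.

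**The case against.** **The analysed larvae may not be the seeded ones.** Only *Ae. aegypti* is added, yet the Secondary outcome section analyses emergence for each of two species, and larvae from positive containers are also reared to adults for identification. Field larvae may therefore form part or all of the denominator. This stands as an uncertainty, and the volume weighting is conditional on it. If field larvae count, weights follow larval numbers instead; they are still unequal, and larvae are still treated as independent.

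**A reader might infer that large containers dominate the rate and hide real transfer.** The documents do not support that. Larvae are tied to the water sample, not to container size, and the sample goes into a bottle of unstated volume that may cap or equalise it. No dose, concentration-response or container size is given. Dilution in more water is plausible physical reasoning, not protocol text. In Step 4 the pooled test still declared a reduction in 77–100% of runs with transfer. Part of that comes from its inflated error rate, but it does not show masking as the main risk, and the no-transfer results err the other way. Nor does the plan say that a non-significant result means the traps failed.

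**Sample volume is laboratory detail that an article may leave to the full protocol.** This is fair, and a fixed volume there would remove the weighting problem. It would not repair the stated larva-level test.

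**Equal weight per container is itself a choice.** It is, and it gives a proportion based on 3 larvae the same weight as one based on 50. It nevertheless answers the question asked, which concerns breeding sites.

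**Conclusion.** The point holds in limited form. As written, the arm-level emergence rate weights containers by the water or larvae they yield, and the chi-squared or Fisher test ignores both container and randomised cluster.

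- **Estimate.** It can be attenuated if collected volume follows container size and the effect is weaker in larger volumes. The size cannot be determined from the documents, and it is nil if a fixed volume is taken. In the simulation the loss ranged from negligible (0.149 against 0.152) to more than half (0.060 against 0.145).
- **Test.** Significance is overstated whenever larvae within a container are correlated. Under the assumed correlation of 0.1, false declarations of a reduction ran at 12–35% against 2.5%. This is the firmer part of the point, because it needs no assumption about dilution.

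The weighting result rests on the density reading of the seeding rule and on the seeded larvae being the ones analysed. Emergence is not among the secondary outcomes listed under Outcomes, and neither the primary outcome nor the ovitrap index depends on it. The point is minor.

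**What to change.** In **Secondary outcome**, replace the larva-level chi-squared or Fisher test. Compute one emergence proportion per container from the added *Ae. aegypti* larvae, and report field larvae separately. Average containers with equal weight within each cluster, and compare the 12 v 12 cluster means between arms.

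In **Monitoring quality of TORS and ADDs post-application**, state a fixed sample volume and a fixed number of added larvae per natural container where the volume allows, as the trap-water test already does ("In each 250 ml ADD water sample, 25 third instar" larvae). Record the volume collected, so that results can also be shown by volume class. If the present rule means one 10 ml sample with one larva per container, say so.

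The cost is a change of laboratory and analysis wording, with no extra samples. Proportions from very small samples will be noisier, and a cluster that never yields a positive container contributes no mean. In Step 4 the cluster-mean test declared a reduction in 80–93% of runs with transfer, and in 2–3% without it.
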